## Description of Investigational product (Amphomul^®^)

Amphomul^®^ is an emulsion formulation of Amphotericin B *(*AMB*),* which is a polyene antifungal antibiotic produced from a strain of *Streptomyces nodosus*. Details of other ingredients of the formulation are mentioned in Section 15.1. Amphotericin B is designated chemically as [1R-(1R’, 3S’, 5R’, 6R’, 9R’, 11R’, 15S’, 16R’, 17R’, 18S’, 19E, 21E, 23E, 25E, 27E, 29E, 31E, 33R’, 35S’, 36R’, 37S’)] –33-[(3-amino-3, 6-dideoxy-beta-d-mannopyranosyl) oxy]–1,3,5,6,9,11,17,37-octahydroxy-15, 16, 18–trimethyl-13–oxo-14, 39–dioxabicyclo (33,3,1) nonatriaconta-19,21,23,25,27,29,31-heptaene-36–carboxylic acid. Its molecular weight is 924.09 and molecular formula is C_47_H_73_NO_17_.

**Mechanism of action:** It acts by binding to sterols in the cell membrane of susceptible fungi, with a resultant change in the permeability of the membrane. It has shown *in vitro* activity against *Asperigillus* and *Candida* with minimum inhibitory concentration generally less than 1 µg/mL. In animal studies, it has shown activity against *Asperigillus fumigatus, Candida albicans, C. guillermondil, C. stellatodae* and *C. tropicallis, Cryptococcus sp., Coccidiodomyces* sp*., Histoplasma* sp. and *Blastomyces* sp., in which the end point was clearance of microorganisms from target organs and prolonged survival of infected animals.

**Pharmacokinetics:** The pharmacokinetics of AMB after IV administration is nonlinear. Volume of distribution and blood clearance increase with increase in dose resulting in less than proportional increase in blood concentration over a dose range of 0.6 to 5.0 mg/kg/day. Extensive clinical studies on AMB suggest it to be effective against various Leishmania species in humans.

## Summary of Preclinical Studies with Amphomul^®^

A detailed description of preclinical data with Amphomul^®^ can be found in the investigator’s brochure (IB). This section will summarize the information shortly.

Pharmacokinetic profile

Male New Zealand white rabbits were tested to evaluate the pharmacokinetic parameters of the AMB formulations.

The pharmacokinetics of AMB after administration as emulsion (Amphomul^®^) is non‑linear. Amphomul^®^ is cleared from plasma at a faster rate than the conventional formulation containing sodium deoxycholate. The volume of distribution and clearance from blood is more than the Conventional formulation.

The pharmacokinetics of AMB after administration as an emulsion (Amphomul^®^) is as follows: (values in parenthesis indicate the pharmacokinetics of AMB deoxycholate)

Peak concentration (µg/mL) - 0.387±0.176 (0.576±0.006*)*

Clearance (mL/hr/kg) - 16.06±12.5 (0.54±0.28)

Apparent volume of distribution (l/kg) - 26.14 ±18.52 (1.47±1.26)

Half-life (Hours) - 6.622 ± 10.63 (1.89 ± 0.73)

AMB levels after administration as emulsion were higher in spleen and liver than as conventional formulation. AMB in emulsion formulation was rapidly distributed to tissues when injected by IV route. The ratio of drug concentration in tissues to drug concentration in blood increased disproportionately with increasing dose, suggesting that the elimination of the drug from the tissues is delayed. Peak blood levels of AMB were lower after administration of AMB emulsion than conventional formulation containing sodium deoxycholate. However, tissue levels of AMB emulsion were found to be higher than the conventional formulation.

Drug interactions

AMB is known to interact with the following drugs, which should be thus administered with caution:

Antineoplastic agents: Concurrent use may enhance potential for renal toxicity.

Corticosteroids: May potentiate hypokalemia.

Cyclosporine: Additive nephrotoxicity.

Digoxin: Nephrotoxicity may decrease digoxin clearance.

Leukocyte transfusions: acute pulmonary toxicity if given concurrently.

Skeletal muscle relaxants: Hypokalemia may potentiate skeletal muscle relaxant activity.

Zidovudine: Increased myelosuppression.

Non-steroidal anti-inflammatory drugs, sulfas, aminoglycosides, and IV contrast dyes in patients with renal insufficiency, except for dehydration due to angiotensin antagonists are well known for their nephrotoxic potential. Thus, antineoplastic drugs, corticosteroids, cyclosporin A, antifungal imidazoles if required could be administered with a close monitoring of the patients.

**Toxicology:**

Following *in vivo* studies were conducted to evaluate the toxicity of AMB emulsion (*In vivo* toxicity studies).

- - 1. **Single dose toxicity in mice:**

It was found that AMB lipid emulsion was less toxic than AMB conventional (AMFOCARE) and Amphotericin lipid complex (ABELCET).

**b) Repeat dose toxicity study in mice**

The AMB lipid emulsion showed less toxicity than AMFOCARE

**c) Single dose toxicity in rats**

The AMB lipid emulsion was less toxic than AMFOCARE.

**d) Repeat dose toxicity study in dogs**

AMB lipid emulsion offers significant protection against hepatotoxicity and nephrotoxicity as compared to Conventional AMB

***In-Vitro* effects of Amphotericin B on Human Cells:**

The *in vitro* toxicity data clearly indicate that AMB emulsion and lipid complex is less toxic than AMFOCARE when the target cells are human RBCs, which is in agreement with reported data (*Tabosa Do Egito, et al, 1996*)

## Clinical Studies

**Amphomul^®^**

A clinical study was carried out in 48 patients at two centers in India comparing safety and efficacy of three different regimens of intravenous AMB emulsion (Amphomul^®^) for treatment naive and treatment resistant cases of Kala-azar.

In this study, three regimens of this formulation were tried viz., 2 mg/kg/day, 3.5 mg/kg/day and 5 mg/kg/day (approximate total dose- 15 mg/kg). The results of this study showed an exceptionally better safety profile and at the same time maintaining a comparable efficacy level in Visceral Leishmaniasis patients.

AMB emulsion did not produce any clinically recognizable hepatic, respiratory or hemodynamic disturbances in any patient. Also significant nephrotoxicity, hypokalemia and hypomagnesaemia that are almost always associated with conventional AMB treatment were conspicuous by their absence.

Overall the new emulsion formulation of AMB demonstrated efficacy similar to lipid/conventional formulations in treatment of Kala-azar. Amphomul^®^ was also found to be safe and well tolerated at doses administered (2, 3.5 and 5, in mg/kg dose) IV on alternate days for three days, with very low incidence of infusion related AEs in patients with Visceral Leishmaniasis.

It also produced excellent cure rates across all three arms, for patients who received the cumulative dose of 15 mg/kg over the specified treatment duration of the previous study.

**Safety Data from previous clinical studies with Amphomul^®^**

More commonly encountered side effects:

Chills, fever, headache, nausea and vomiting, loss of Appetite, diarrhoea, stomach pain, hypokalemia, hypoxia.

Less commonly encountered side effects:

Anaemia, leucopoenia, renal function impairment, respiratory distress, thrombocytopenia, back pain, chest pain, dark urine, jaundice, skin rash, anaphylactic reaction, dyspnoea, hypertension, hypotension, tachycardia, facial edema, hives, itching, skin redness, unusual tiredness, weakness.

The association of the above adverse reactions with AMB emulsion is uncertain.

**AmBisome:-**

Liposomal Amphotericin B is approved in several European countries for primary treatment of Visceral Leishmaniasis, and the U.S. Food and Drug Administration had approved it, recommending a total dose of 21 mg/kg; however, in a pilot trial in Indian Visceral Leishmaniasis, liposomal Amphotericin B (AmBisome) in cumulative doses of 6, 10, and 14 mg/kg cured all 10, 9, and 10 patients, respectively.

In the randomized, double-blind, dose-ranging, multicenter trial, 84 patients with Visceral Leishmaniasis refractory to antimony therapy were administered AmBisome at cumulative doses of 3.75, 7.5, and 15.0 mg/kg for 5 consecutive days. Posttreatment apparent cure and definitive cure were assessed at 2 weeks and 6 months after the end of therapy, respectively. Low-dose liposomal Amphotericin B (AmBisome) given for 5 days can cure most patients with Indian kala-azar. The shortened duration of treatment reduces the usual hospital stay from 5 weeks or more to just 5 days. The shortened hospital stay will further reduce the hospital cost and the person-days lost for both patients and attendants, and it will increase the availability of hospital beds 6- to 7-fold. The decreased number of infusions from 15 or more to 5 reduces the costs of fluids, tubing, and other hospital supplies. Although clinical availability of AmBisome is a major therapeutic advance in the treatment of leishmaniasis, it may remain out of reach of most patients with Visceral Leishmaniasis because of its higher cost (*Sundar S et al, 2002*).

AmBisome at a total dose of 20 mg/kg is safe and effective under routine programme conditions in Bihar. Treatment with a lower dosage would reduce patient hospitalization time by half and save a considerable amount of resources. Various Phase 2 studies using AmBisome at 15 mg/kg have showed good efficacy and safety outcomes, but this dosage has not yet been proven effective under routine programme conditions (*Gupta J et al, 2008*)

## Rationale for the study

Due to the high incidence of drug resistance, drug toxicity and long duration of treatment (required by Sodium Stibogluconate), AMB is increasingly being used as first line treatment of Kala-azar (*Chandra J, 1995*; *Thakur CP, 1998*; *Thakur CP, 2001*). Amphotericin B deoxycholate treatment results in 100% cure, even in Antimony resistant cases (*Thakur CP, 1993*; *Thakur CP, 1999*). Unfortunately, Conventional AMB needs to be administered over 20 to 30 days and causes significant nephrotoxicity (*Thakur CP, 1999*; *Bennet JE, 2001*).

Despite the value of AMB and the importance of early use to prevent emergence of resistant cases and achieve rapid cure, it has often been underutilized in clinical practice. This is because of its unfavorable toxicity profile.

The lipid emulsion form of AMB has been proven to produce dramatically different pharmacokinetic properties. Preclinical and clinical studies have shown it to be better tolerated than conventional drug.

In continuation with Section 9.5 above, it is of obvious scientific interest to further attempt to shorten the duration of treatment with Amphomul^®^. This will reduce the cost of hospitalization and the resulting burden on the healthcare system in developing countries like India. The previous study (BSV-AMBE II-KA-0706) had shown that Amphomul^®^ at the single bolus dose infusion of 15 mg/kg is safe and effective in the treatment of Kala-azar. Amphotericin B emulsion, administered as a 15 mg/kg single bolus dose infusion, had produced excellent initial cure, clinical improvement and definitive cure rates in subjects with treatment naive cases of visceral leishmaniasis (Kala-azar). This study demonstrated higher outcome score of efficacy with Amphotericin B emulsion as a single‑bolus infusion as compared to the study drug given in divided doses. Amphotericin B emulsion did not produce any clinically recognizable hepatic, renal, respiratory or hemodynamic disturbances in any subject. Analysis of vital parameters confirmed absence of any adverse effect of Amphotericin B formulation on hemodynamic parameters at daily doses as high as 15 mg/kg given either on Day 1 as a single-bolus infusion. Overall Amphotericin B emulsion was well tolerated with very low incidence of infusion related AEs.

Hence, on the basis of the results of above Phase II study, Bharat Serums and Vaccines Ltd had decided to go a step forward by doing a prospective, randomized, open-label, multicentric Phase III clinical study of Amphotericin B lipid emulsion. The main aim of the Phase III study will be to demonstrate that low cost, infusion of Amphomul^®^ 15 mg/kg/day is safe and well tolerated in the treatment of Visceral Leishmaniasis (Kala‑azar) as compared to AmBisome.

10. STUDY OBJECTIVES and ENDPOINTS

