## OBJECTIVES

### Primary

To compare and evaluate efficacy of Amphotericin B emulsion (15 mg/kg/day as a single dose infusion) compared to AmBisome (15 mg/kg as a single dose infusion) in the treatment of Visceral Leishmaniasis (Kala‑azar)

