### Secondary

To assess the safety of infusion of Amphotericin B emulsion (15 mg/kg as a single dose) compared to AmBisome (15 mg/kg as a single dose infusion) in treatment of Visceral Leishmaniasis (Kala-azar).

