**Other AEs**

Other AEs would be appropriately graded based on the NCI-CTC-AE-v3 criteria. These would be statistically analyzed to know the safety of Amphotericin B emulsion compared to AmBisome along with the following categories -

- Incidence of AEs by preferred term (used from MedDRA)
- Incidence of AEs by system organ class
- Incidence of related/unrelated AEs
- AEs irrespective of causality
- Number of patients experiencing an AE at least once
- Display of severe AEs

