### Safety Analysis

Safety Endpoints:

- - Incidence of DLTs
  - Incidence of IRTs
  - Incidence of nephrotoxicity and hepatotoxicity
  - Incidence and frequency of AEs and SAEs (including laboratory abnormalities)

The safety analysis will be performed on the ITT population. Proportion of patients experiencing DLTs, IRTs, nephrotoxicity, hepatotoxicity, AEs and SAEs will be tabulated. Laboratory data will be summarized and displayed, including abnormal values judged to be clinically significant.

SAE reports will be presented individually. AE data will be listed individually, coded using Medical Dictionary for Regulatory Activities (MedDRA) enhanced version. Each AE will be counted only once for a given patient. If the same AE occurs on multiple occasions, the highest severity and relationship will be assumed. If two or more AEs are reported as a unit, the individual terms will be reported as separate experiences.

Concomitant medications will be coded by using the World Health Organization Drug Dictionary (WHODD) Reference List enhanced version.

Vital sign data, physical examination results, ECG examinations results will be summarized for ITT population

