### Statistical Analysis of Data

SIRO Clinpharm Pvt. Ltd will perform the statistical evaluation using appropriate statistical tests. Statistical analysis will be performed using SAS^®^ software (SAS Institute Inc., NC, USA).

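### Section 9.6 makes demonstrating comparative safety the main aim, against the protocol's own objectives, sample size and margin, and the stated safety analysis cannot support that claim

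*Protocol*

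**What the plan says.** Four parts of the protocol bear on this.

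- **Aim.** Section 9.6 ends its rationale with "The main aim of the Phase III study will be to demonstrate that low cost, infusion of Amphomul^®^ 15 mg/kg/day is safe and well tolerated"; the comparison it names is with AmBisome. That sentence does not mention efficacy.
- **Objectives.** Section 10.1.1 gives the primary objective as "To compare and evaluate efficacy of Amphotericin B emulsion (15 mg/kg/day as a single dose infusion) compared to AmBisome". Section 10.1.2 gives the secondary one as "To assess the safety of infusion of Amphotericin B emulsion (15 mg/kg as a single dose) compared to AmBisome". The study summary (section 8) ranks them in the same way.
- **Size and decision rule.** Sections 11.2 and 12.1 size the trial on the difference in definitive cure, with a margin of -0.10 and at least 80% power. Section 20.2.2 accepts non-inferiority only if the lower limit of the two-sided 95% confidence interval lies above -0.10. It also plans two-sided 95% intervals for the initial cure and clinical improvement proportions.
- **Safety analysis.** Section 20.2.3 says: "Proportion of patients experiencing DLTs, IRTs, nephrotoxicity, hepatotoxicity, AEs and SAEs will be tabulated". Section 18.6, under Other AEs, adds: "These would be statistically analyzed to know the safety of Amphotericin B emulsion compared to AmBisome along with the following categories". Section 20.2.4 says in general terms: "SIRO Clinpharm Pvt. Ltd will perform the statistical evaluation using appropriate statistical tests". Section 18.6 calls nephrotoxicity the main criterion for the analysis of safety.

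**The concern.** A claim to demonstrate that one drug is safe compared with another needs a comparative estimate and some statement of how much worse the new drug could still be. The protocol handles definitive cure in this way. It does not do so for safety, although section 9.6 calls comparative safety the main aim.

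Two things are at stake. First, the protocol gives two different answers to what the trial is for, and a report could cite whichever suits the result. Second, with at most 125 patients on AmBisome, bare percentages for an uncommon event can look alike, or differ without reaching significance, while a material excess on Amphomul remains compatible with the data. A report that then repeated the wording of section 9.6 would claim more than the design supports.

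**Working it through.** **1. The stated size, and what it serves.** Inputs are from section 11.2: 400 evaluable patients (300 and 100) and about 20% loss.

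- 400/0.8 = 500, 300/0.8 = 375 and 100/0.8 = 125, so the enrolment figures reproduce.
- The 400 follows from the non-inferiority formula for cure. The number on AmBisome is (1.960 + 0.842)² × p(1-p) × (1 + 1/3) / 0.10².
- At p = 0.90 this gives 95 on AmBisome, 380 in all. At p = 0.89 it gives 103, 412 in all. A cure rate near 0.893, which the protocol does not state, would give 400.
- No safety rate, margin or power enters this calculation.

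**2. The statements side by side.**

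| Place | Leading question | Criterion |
| --- | --- | --- |
| 9.6 | Demonstrate safety compared with AmBisome | None |
| 10.1 | Efficacy primary; safety secondary, to be assessed | None |
| 11.2, 20.2.2 | Definitive cure | Lower 95% limit above -0.10 |
| 20.2.3 | Safety | Tabulated proportions |

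The only numerical safety threshold is the dose-limiting toxicity rule (more than 33%) in sections 8 and 13. It applies to the overall percentage in the study and stops recruitment. It does not compare the arms.

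**3. Illustration of what this size can show.** The safety set is all dosed patients (sections 20.1 and 20.2.3), so at most 375 and 125. The event rates and the test below are assumptions, because the protocol gives neither for nephrotoxicity. Power is the sum, over all pairs of binomial counts, of their joint probability where the two-sided Fisher p is below 0.05 and the Amphomul rate is the higher. The miss rate is 1 minus power.

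| AmBisome | Amphomul | Power | Missed |
| --- | --- | --- | --- |
| 0% | 4% | 82.1% | 18% |
| 0.5% | 4.5% | 60.6% | 39% |
| 1% | 5% | 48.9% | 51% |
| 2% | 6% | 37.4% | 63% |

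The choice of test matters less than the assumed rate. For 1% against 5%, the uncorrected chi-square has power 53.6% and the normal approximation 50.9%. The continuity-corrected chi-square is lower, at 37.3%.

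**4. One possible result.** Take 15/375 (4.0%) against 1/125 (0.8%), a difference of 3.2 points. Fisher p = 0.137. The Wilson 95% limits are 2.44% to 6.49% on Amphomul and 0.14% to 4.39% on AmBisome. The Newcombe limits follow, in percentage points:

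- upper: 3.2 + √[(6.49 - 4.0)² + (0.8 - 0.14)²] = +5.8
- lower: 3.2 - √[(4.0 - 2.44)² + (4.39 - 0.8)²] = -0.7

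The observed rate is five times higher on Amphomul (4.0/0.8), the test is not significant, and an excess of nearly 6 points is not excluded. The table of proportions alone does not show that last fact.

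**5. The interval is useful at this size.** With equal observed rates, the Newcombe upper limit is +1.7 points at 3/375 against 1/125 and +3.4 points at 15/375 against 5/125.

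**The case against.** The strongest reply is that section 9.6 is background. The operative text is consistent: efficacy is primary, safety is assessed as a secondary objective, and the size and decision rule concern definitive cure. Descriptive safety tables fit an objective to assess, which needs no margin. The phrase comparing with AmBisome may only name the comparator. The form of the safety tables could also be settled in a statistical analysis plan that is not shown.

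Much of this stands. The formal objectives need no safety hypothesis, and the choice of test or interval may properly be left to a later plan. What does not fall away is that the protocol itself calls demonstrating comparative safety the main aim, in conflict with its own section 10.1. A later analysis plan would not remove that sentence.

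A reader might also infer that the trial will treat a non-significant difference as proof of safety, and will therefore overlook a rise in nephrotoxicity from 1% to 5% about half the time. The protocol does not support that reading. It states no such rule and names no difference test for nephrotoxicity, which it plans only to tabulate. The reference to statistical analysis in section 18.6 stands under Other AEs. The figure of about half belongs to one assumed pair of rates, and for the same 4-point rise the miss rate runs from 18% to 63%.

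**Conclusion.** The point holds as an inconsistency within the protocol with a consequence for reporting. The main aim in section 9.6 is not the aim that the trial ranks first, is sized for or has a decision rule for. Tabulated proportions give no measure of the excess excluded, so they cannot support a claim that comparative safety was demonstrated.

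The contradiction rests on the text alone. The numerical illustration rests on assumed event rates, a two-sided Fisher test at 0.05 and all 500 patients dosed; with fewer dosed, the miss rates would be higher. The primary efficacy analysis is not affected. The change should be made, but it is a matter of wording and presentation and does not call for a redesign.

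**What to change.** 1. **Section 9.6.** Reword the main aim to agree with section 10.1, for instance: to show that Amphomul is non-inferior to AmBisome in definitive cure, and to estimate its safety relative to AmBisome.
2. **Section 20.2.3.** For nephrotoxicity, hepatotoxicity, DLTs, IRTs and SAEs, tabulate the proportions with the difference (Amphomul minus AmBisome) and its two-sided 95% confidence interval, for example by Newcombe's method. State that comparative safety will be described by the upper limit of that interval.

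The cost is two changes of wording and one more column in the safety tables, with no more patients or data. The downside for the sponsor is that the report can say only how large an excess is excluded, not that comparative safety was demonstrated.

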## OBJECTIVES

### Primary

To compare and evaluate efficacy of Amphotericin B emulsion (15 mg/kg/day as a single dose infusion) compared to AmBisome (15 mg/kg as a single dose infusion) in the treatment of Visceral Leishmaniasis (Kala‑azar)

### Secondary

To assess the safety of infusion of Amphotericin B emulsion (15 mg/kg as a single dose) compared to AmBisome (15 mg/kg as a single dose infusion) in treatment of Visceral Leishmaniasis (Kala-azar).

## ENDPOINTS

### Primary

- Proportion of patients with Amphomul^®^ 15 mg/kg as a single dose infusion achieving
  - Initial cure (splenic aspirate score 0 on Day 30 or on Day 45)
  - Clinical improvement on Day 30 after study drug administration.
    - Absence of fever; and >1 out of following:
      - Increase in hemoglobin concentration by >10% compared to baseline
      - Weight gain compared to baseline
      - Decrease in spleen size by >33% compared to baseline
  - Definitive cure

1. Initial cure at Day 30 or Day 45
2. No signs and symptoms of relapse of Kala-azar for 6 months after study drug administration. If signs and symptoms of relapse of the disease are suspected at any time during the 6 months follow up, splenic aspirate shall be performed at 6 months or earlier after study drug administration.

Proportion of patients achieving all three-efficacy endpoints will be compared across the two groups.

